Transfer learning will provide faster and more effective learning algorithms by reducing the size of the dataset. The network will be fine-tuned with transfer learning, and feature extraction will be performed quickly. The dataset will be expanded using smaller time windows of the signals. If we divide 330 min of recordings into 10-s segments, 1980 time series or representative images will be processed for each measurement. In addition, the dataset can be expanded using the data augmentation technique. Data from 36 subjects would be sufficient in this case. Of the dataset, 70% will be used for training the neural network, 15% for validation, and 15% for testing. To ensure that the training and test sets are created on an individual basis, we would need a larger number of participants. This could be the subject of future studies.

Despite their excellent performance, deep learning models produce good results without being able to explain why. These models act as a black box for users. This is one of the main limitations of deep learning in medicine. Therefore, the issue of the explainability of neural networks has emerged (Ilias and Askounis, 2022; Ong et al., 2021; Thibeau-Sutre et al., 2023). The behavior and reasons for the importance of features automatically used in artificial intelligence tools will thus be understood (Ong et al., 2021). The XAI framework will use different techniques, such as LIME (Local Interpretable Model-agnostic Explanations), Occlusion Sensitivity, and Grad-CAM. These methods, each with a specific approach to classifying an image, produce a map showing the regions of the image that are important for the process. The network will use these maps for decision-making.

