#### Inclusion criteria

3.1.1

Young earthquake survivors without specific diseases who recently experienced the earthquake in our region in February 2023 will be selected. The sample sizes of 20–25 participants have been selected in similar studies (Maheu et al., 2005; Nakajima et al., 2016; Tegeler et al., 2023; Zabrecky et al., 2020). The sample size selected (*n* = 10–12 participants per group) follows the rule of thumb proposed by Julious (2005), which is widely recognized in the methodological literature as a minimum standard for pilot studies (Julious, 2005). Furthermore, our proposal will use deep learning and current artificial intelligence algorithms. Because data can be obtained from each measurement within the time-series dataset used for this purpose, a substantial amount of data can be generated through windowing and data augmentation, and transfer learning can be performed; it is assumed that a dataset from 36 participants will be sufficient. Consequently, at least 30 university students aged between 20 and 25 years who experienced and survived the earthquake will take part in the experiment. They must have experienced the earthquake as a significant and severe event. In accordance with the inclusion criteria, the participants will be healthy, non-obese men (*n* = 18) and women (*n* = 18). In particular, all participants should have experienced the earthquake disaster in the local region. All participants must be free of any chronic or acute infection, neurological, psychiatric, and/or cardiovascular disease. They must be non-smokers, have no alcohol or drug addiction, and not be under any medical treatment. Pregnant or breastfeeding women will not be included in the study.

University students who survived the earthquake in the region will be invited to volunteer for this study. The inclusion and exclusion criteria will be verified by interviewing the volunteers. Participants will then undergo a medical examination by a psychiatrist. If no problems are found, participants will be recruited for the study.

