#### ECG, EDR, and fNIRS data

3.4.2

The data obtained using deep learning techniques will be classified. Classification studies will be performed with deep learning to emphasize to characterize differences between the control and treatment groups, as well as differences before and after treatment within groups and to show that the difference is significant. The data will be converted into spectrogram images and processed as time-series data. A suitable pretrained network (AlexNet, SqueezeNet, GoogLeNet, etc.) will be used with transfer learning, and classification will be performed. Technical information is provided in our published articles (Özcan and Alkan, 2021, 2023a, 2023b).

On the other hand, correlation analysis will be performed using deep learning method (Alessandrini et al., 2023). Then, the features used in the classification will be evaluated using explainable artificial intelligence techniques.

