#### Performance metrics

3.5.3

The proposed methods’ accuracy, sensitivity, specificity, precision, and F1-score (Table 2) will be measured as evaluation parameters. A confusion matrix will also be extracted to provide an overview. An optimization study will be performed to determine the best hyperparameter settings. Five cross-validation will be selected, and the average values of the results will be obtained. The methods with the highest performance will be compared with the others.

**Table 2 tab2:** Calculations of performance metrics (Özcan and Alkan, 2021, 2023a, 2023b).

Accuracy	Sensitivity	Specificity	Precision	F1 score
$\frac{\mathrm{TP}+\mathrm{TN}}{\mathrm{TP}+\mathrm{TN}+\mathrm{FP}+\mathrm{FN}}$	$\frac{\mathrm{TP}}{\mathrm{TP}+\mathrm{FN}}$	$\frac{\mathrm{TN}}{\mathrm{TN}+\mathrm{FP}}$	$\frac{\mathrm{TP}}{\mathrm{TP}+\mathrm{FP}}$	$\frac{2\mathrm{TP}}{2\mathrm{TP}+\mathrm{FP}+\mathrm{FN}}$

TP: true positive; FN: false negative; FP: false positive; TN: true negative.

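### Training and test data for the deep-learning classifiers share participants, so control-versus-treatment accuracy can be high with no arm effect

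*Protocol article*

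**What the plan says.** Section 3.5.2 (Methods for deep learning) describes how the dataset is built: "If we divide 330 min of recordings into 10-s segments, 1980 time series or representative images will be processed for each measurement". Augmentation may enlarge it further. The split follows: "Of the dataset, 70% will be used for training the neural network, 15% for validation, and 15% for testing". On separating people between the sets, the section says "To ensure that the training and test sets are created on an individual basis, we would need a larger number of participants", and adds "This could be the subject of future studies".

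Sections 3.4.1 and 3.4.2 set two classification targets: control against treatment, and before against after treatment within a group. Section 3.4.2 gives part of the purpose as "to show that the difference is significant". Section 3.5.3 (Performance metrics) adds "Five cross-validation will be selected, and the average values of the results will be obtained" and states no grouping by participant.

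Section 3 describes a non-randomised parallel-group study with allocation in order of enrolment. Section 3.1.1 supports the sample size partly on the ground that "a substantial amount of data can be generated through windowing and data augmentation". Section 5 (Limitations) again expects 36 participants to suffice for deep learning, because of transfer learning. It does not list the overlap of people between training and test data.

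**The concern.** In a parallel-group study every window from one participant carries the same arm label. If some of that participant's windows train the network and others test it, the network need not learn anything about the intervention. It only has to recognise that person's ECG, skin-conductance or fNIRS pattern and return the arm already seen with it. The test windows then measure, at least in part, how recognisable people are.

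The between-arm classification result is what is at stake. Accuracy, sensitivity, specificity, precision and F1 would be inflated to an unknown degree, and the explainability maps would describe the features of the same classifier. For the between-arm question the independent units are the 30 to 36 people, not the windows. A statement of significance resting on window-level performance would have no valid basis.

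**Working it through.** **Inputs from the protocol article.** 330 min of measurement per participant, 10-s windows and a 70/15/15 split (section 3.5.2); 36 participants (Table 1, section 3.5.2); 10 to 12 per group (section 3.1.1); 10 control and 20 intervention (section 3.1.2).

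**Assumed, not in the article.** The share of feature variance lying between people, taken from 0 to 0.7.

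**1. The article's own figure.** 330 × 60 / 10 = 1,980 windows per participant. It reproduces.

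**2. Overlap under a random window split.**
- Total: 36 × 1,980 = 71,280 windows per signal. This is an upper figure for the between-arm comparison, because section 3.4.1 places that classification during mental stress, which is only part of the recording.
- Split: 0.70 × 71,280 = 49,896 for training; 0.15 × 71,280 = 10,692 each for validation and test.
- Per person, on average: 0.70 × 1,980 = 1,386 training and 0.15 × 1,980 = 297 test windows.
- Chance that a given person has no training window: about 0.3^1980, roughly 10^−1035. In effect everyone tested has also been trained on.

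**3. What this does when there is no arm effect.** A null simulation used 10 Gaussian features with person-specific means, 200 windows per person, a 5-nearest-neighbour classifier and 40 replicates. Mean balanced accuracy was:

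| Between-person share (assumed) | 0 | 0.1 | 0.3 | 0.5 | 0.7 |
|---|---|---|---|---|---|
| 12 vs 12, window split | 0.50 | 0.54 | 0.66 | 0.83 | 0.96 |
| 12 vs 12, grouped five-fold | 0.50 | 0.50 | 0.50 | 0.51 | 0.51 |
| 10 vs 10, window split | 0.50 | 0.54 | 0.68 | 0.84 | 0.96 |
| 10 vs 10, grouped five-fold | 0.50 | 0.50 | 0.50 | 0.50 | 0.48 |
| 12 vs 24, window split | 0.50 | 0.52 | 0.62 | 0.78 | 0.94 |
| 12 vs 24, grouped five-fold | 0.50 | 0.50 | 0.50 | 0.50 | 0.50 |

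At a share of 0.7 with 12 versus 12, the standard deviation over replicates was 0.016 for the window split and 0.076 for grouped folds. The window split is therefore biased and also looks more precise than 24 people can support.

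**4. Is a participant-level evaluation feasible?** Five folds hold out 36/5 = 7.2 or 30/5 = 6 people each, including 12/5 = 2.4 or 10/5 = 2 controls. A single 70/15/15 split of 36 people would give 25.2/5.4/5.4.

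**5. Reference values.** Always predicting treatment in the pooled comparison gives plain accuracy of 24/36 = 20/30 = 67%, but balanced accuracy of (100% + 0%)/2 = 50%.

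**The case against.** The article never says in so many words how windows are assigned, so a window-level split is an inference. It is still the natural one: the data are cut into windows, that dataset is divided by percentages, and sets formed by individual are deferred.

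The reason given for deferral has some force. A single participant-level 70/15/15 split would leave about five people, roughly two of them controls, in the test set. That is an argument against a single split. Grouped cross-validation uses every participant for testing once and is feasible at this size, with wide uncertainty.

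The simulation shows direction and plausible range, not the size to expect here. Its classifier is simple; section 3.4.3 gives such classifiers low priority, and the planned networks are CNNs and LSTMs. With no between-person variance there is no inflation, and at 0.1 there is little.

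A reader might also infer that before-versus-after labels leak in the same way. They do not: each person carries both labels, so identity alone does not reveal the label. Adjacent windows and shared session conditions can still link training and test data, but that is a different mechanism and was not simulated.

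A reader might see the five-fold scheme as contradicting the 70/15/15 split. The article does not say how the folds relate to the held-out set, and the two can coexist, so no contradiction is established.

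Finally, the sentence on significance names no test or p-value, and the study calls itself preliminary. Both are true, but the stated purpose remains, and the admission about individual-level sets is not carried into the interpretation or the limitations.

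**Conclusion.** The concern holds for the control-versus-treatment classification. As planned, that analysis can score well above chance with no arm effect, and it cannot support a statement that the arms differ significantly. Under the assumptions shown, null balanced accuracy ranges from 0.50 to 0.96 with equal arms of 12 and from 0.50 to 0.94 with 12 versus 24, against about 0.50 when folds are grouped by participant. Where this trial would fall depends on the between-person variance share and on the networks used, neither of which can be fixed from the article.

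Two limits apply. Before-versus-after classification is less exposed. The trial's main result is not undermined, although a reader might infer that it is: section 3.5.1 names RMSSD, HF and LF as primary pilot outcomes, analysed by a linear mixed model or ANCOVA, and these do not pass through the classifier.

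**What to change.** - **Splitting.** For all classification analyses, use five-fold cross-validation grouped by participant and stratified by arm, or leave-one-participant-out. Keep all windows and augmented copies of a person in one fold. Do normalisation, augmentation and hyperparameter tuning inside the training participants only.
- **Reporting.** Give balanced accuracy against 50%, or plain accuracy against the majority-class rate (67% for pooled treatment versus control), with uncertainty computed at participant level.
- **Significance.** Either base any such statement on permuting arm labels across participants, saying that exchangeability is an assumption under non-randomised, chronological allocation, or delete that purpose from section 3.4.2.
- **Wording.** Replace the section 3.5.2 sentence that individual-level sets need more participants. Also replace the statements in sections 3.1.1, 3.5.2 and 5 that 36 people suffice for deep learning because of windowing, augmentation or transfer learning. Say instead that the effective sample for the between-arm question is 30 to 36 people.

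Section 3 reports that data collection was completed by 30 June 2025; these changes need no new data, only code, wording and some extra computing, mostly for retraining under permutation. Reported accuracy is likely to be lower and its intervals wider, since each fold holds out only about two controls.

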Deep learning techniques and statistical analyses will be used to examine the causality between the generated stress, given warning, and measurements. The data will be processed as a time series or converted into images in our study. Each participant will have 390 min of experimental activity, including 330 min of measurement time.

Transfer learning from an existing pretrained convolutional neural networks (CNNs) will be applied for the acquired data. If there is sufficient data to train a new neural network, the formation of a new network architecture is considered for the sustainability of the protocol.

Explainable artificial intelligence techniques will be used to analyze the data attributes used by the network.

Below are the protocol diagrams to be applied before the first session, throughout the 10 intervention sessions, and after 4 weeks (Figures 1–3).

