#### Phonocardiogram data and fNIRS data

3.4.1

Heart sounds to be used as stimuli and for monitoring purposes will be converted into Mel spectrograms and input into neural networks trained with sound (OpenL3, YAMNet, and VGGish), and transfer learning will be performed.

Cognitive assessment will be performed by analyzing fNIRS signals to assess activation in specific brain regions (right, center, and left). The details are provided below. During mental stress, classification analyses will be performed between the results between the control and treatment groups and between the results of the same group before and after treatment. Then, using explainable artificial intelligence (XAI) techniques, the temporal and frequency-domain characteristics associated with these changes will be evaluated.

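### XAI maps are to describe arm and before/after differences, but training and test data are not separated by participant, so the maps may show who the person is rather than a treatment change

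*Protocol article*

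**What the plan says.** Section 3.4.1 sets two contrasts for the networks: "classification analyses will be performed between the results between the control and treatment groups and between the results of the same group before and after" (that is, around the intervention). It then says that, "using explainable artificial intelligence (XAI) techniques, the temporal and frequency-domain characteristics associated with these changes will be evaluated". Section 3.4.2 repeats the pattern for ECG, electrodermal and fNIRS data. Classification is meant "to show that the difference is significant", after which "the features used in the classification will be evaluated using explainable artificial intelligence techniques".

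Section 3.5.2 names the techniques, "such as LIME (Local Interpretable Model-agnostic Explanations), Occlusion Sensitivity, and Grad-CAM", and says that they mark the parts of an image that matter. It closes with "The network will use these maps for decision-making". The same section cuts 330 minutes of recording into 10-second segments (1980 per measurement) and splits the data 70/15/15. It states that building the training and test sets by individual would need more participants and may be left to later studies.

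Section 3.5.3 lists accuracy, sensitivity, specificity, precision, F1 and a confusion matrix, averaged over five-fold cross-validation. It names no chance level and does not say whether folds are formed by segment or by participant.

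**The concern.** A saliency map describes what a trained network relied on. It describes treatment only if the network relied on something that treatment changed. When segments from one person lie in both training and test data, the network has an easier route. It can learn the stable features of each person's heart sound, ECG or haemodynamic signal and attach that person's arm to them. Test accuracy then rises above chance although the arms do not differ, and the map marks the features that identify people.

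The before/after contrast has a similar weakness. Segments of the same recording can fall on both sides of the split, so a network can learn the peculiarities of that recording.

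At stake is the physiological reading of the deep-learning part. As written, that reading could be reported as time and frequency signatures of the intervention, backed by good test metrics, with no treatment effect behind it.

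**Working it through.** **The plan's own figure.** 330 min × 60 s / 10 s = 1980 segments per participant and measurement. This agrees with section 3.5.2.

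**What a 70/15/15 split of segments means.**
- 36 participants: 36 × 1980 = 71,280 segments, of which 15% = 10,692 are for testing.
- 30 participants (the arm sizes in section 3.1.2): 30 × 1980 = 59,400, of which 15% = 8,910 are for testing.
- If segments are allocated at random, each person supplies about 0.70 × 1980 = 1386 training segments and 0.15 × 1980 = 297 test segments. Nearly every test segment then comes from a person the network has already seen under the same arm label.
- Split by participant instead, 15% is only 0.15 × 36 = 5.4 people (4.5 of 30).

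**Can accuracy exceed chance with no effect?** The article gives no variance figures, so this was simulated under assumptions: two arms of 12, 100 segments per person, 40 features, a ridge linear classifier, no arm effect and 300 replicates. The between-participant SD is in units of the within-participant SD. The participant-level column holds out two people per arm.

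| Between-participant SD | Segment-level test accuracy | Held-out-participant accuracy | Largest weight / mean weight |
|---|---|---|---|
| 0 | 0.50 | 0.50 | 3.04 |
| 0.5 | 0.71 | 0.51 | 3.09 |
| 1.0 | 0.85 | 0.50 | 3.07 |

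Once people differ, the segment-level split reports 0.71 to 0.85 with no arm effect, while new participants are classified at chance. The largest weight is about three times the mean in every row, so an importance profile looks equally structured whether the classifier is at chance or is recognising people. The weights of a linear model stand in here for a saliency map. The simulation shows the mechanism and does not predict this trial's accuracy.

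**Would a single small participant-level test set do?** With five held-out people and two equally likely classes, chance gives at least 4 of 5 correct with probability (5 + 1)/32 = 0.19, and 5 of 5 with probability 1/32 = 0.03. That is too coarse. Five folds grouped by participant hold out 36/5 = 7.2 people at a time (30/5 = 6) and test everyone once.

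**The reversed sentence.** The description of the methods in section 3.1.2 says "Explainable artificial intelligence techniques will be used to analyze the data attributes used by the network", and sections 3.4.1 and 3.4.2 place the maps after classification. Only the last sentence of section 3.5.2 makes the maps an input to the decision.

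**The case against.** Several points on the other side stand.

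- A reader might infer from "The network will use these maps for decision-making" that the maps are fed back into the network. No architecture or step in sections 3.4 and 3.5 does this, and the other statements give the maps their usual after-the-fact role. It is best taken as a slip. It needs correcting but changes no analysis by itself.
- A reader might also infer that a network at chance would yield a treatment story unnoticed. The metrics and cross-validation in section 3.5.3 would show such a network. The case they would miss is the network that scores well by recognising people.
- A reader might infer that the trial's main result depends on the maps. It does not. Section 3.5.1 makes RMSSD, HF and LF the primary pilot outcomes, analysed by linear mixed model or ANCOVA, and section 5 calls the study preliminary.
- A reader might suspect that a few people dominate averaged maps by sheer number of segments. Planned recording time is the same for everyone, so segment counts alone do not cause this.
- Permutation tests and map checks are details that an article may leave to a fuller plan, so their absence alone would be no finding.

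The last point does not dispose of the matter. The lack of participant-level separation is a stated choice, and so is the use of classification to show a significant difference and of the maps to characterise it. Those statements conflict whatever a fuller plan contains. The article's reason, too few participants, applies to a single 15% test set. It does not apply to grouped cross-validation, which needs no extra recruitment.

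**Conclusion.** The concern holds for the deep-learning part. With training and test data not separated by participant, above-chance accuracy on arm is not evidence of a treatment difference, and maps from such a network cannot be read as characteristics of one. The size depends on how distinct participants' signals are, which the article does not report. Under the assumed range of 0.5 to 1.0 within-participant SDs, null accuracy was 0.71 to 0.85. With no between-participant differences the inflation disappears. The conclusion assumes that segments from one person can fall on both sides of the split, as section 3.5.2 implies, and that the folds in section 3.5.3 are formed the same way. The primary analysis is not touched. The revision should be made before any map is interpreted.

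**What to change.** 1. In section 3.5.3, form the five folds by participant (about 7 of 36 held out each time, everyone tested once) and compute maps only on held-out participants.
2. Read maps as treatment-related only for models whose participant-level performance beats a label-permutation null. Permute arm labels between participants for the arm contrast and session labels within participants for the before/after contrast. Average maps within each participant first and then across participants.
3. Label the maps exploratory in sections 3.4.1 and 3.4.2.
4. Reword the last sentence of section 3.5.2 to say that the maps show the regions the trained network used.

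Comparing the maps with those of networks trained on permuted labels is a useful option but not essential.

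The cost is computing time, since networks must be retrained on permuted labels across signals and contrasts. With 10 to 12 people per arm it is possible that no network beats the null, and then no map is interpreted. No further recruitment is needed.
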